### Adoption and Implementation

Adoption will be examined according to the prevalence of uptake and promotion of the study by primary care, secondary care, social care, and third sector organizations. Implementation will be examined in four ways: (1) a quantitative analysis of patterns of acute use of BWW from baseline to 6 weeks according to clinical and sociodemographic factors; (2) an economic evaluation; (3) long-term effects will also be explored using qualitative interviews and patterns of use of data from the websites. An analysis of barriers and drivers of participants, public and patient groups, and health professionals to reach, adoption, effectiveness, and maintenance of BWW using digitally recorded and thematically analyzed individual qualitative interviews; and (4) textual analysis of written comments made by participants and qualitative interviews to explore the process of self-management, peer support, and organization of care on BWW.

### Health Economics

The study will be conducted from an NHS and societal perspective, which will include cost to the individual but will in addition to clinical outcomes measure the participant's own health status using the SF12-v2 during participant interviews [28]. Thus, the study results will be reported in terms of cost-effectiveness and cost-utility. A detailed resource profile will be established for the intervention versus usual care. The resource profile will include capital costs, for example, the technology, licensing agreements, and assumptions around the length of life of the respective Internet technologies and participant costs in each arm (eg, time accessing the Internet). Economic data will be collected using the economic resource proforma (the Client Service Receipt Inventory [37]), which was piloted successfully in a previous study [38]. Economic data around service use will be collected at baseline, and further economic data, including any time lost from work or usual activities, will be collected during interviews with 200 participants at 12 and 26 weeks who consent to be interviewed. Medication costs will be obtained from the British National Formulary, primary care contacts assigned using community and hospital-based costs from NHS reference costs. Information collected from participants will include any time lost from work or usual activities. An incremental cost-effective ratio and cost-effectiveness acceptability curves will be produced for the BWW versus Moodzone sites. This use of this probabilistic analysis is recommended in NICE guidelines and is economically more useful than classical probability estimates of significance.

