### Objectives

The objectives for this study (known as “the REBOOT study”) are bound within the RE-AIM framework:

Reach: To determine the number and representativeness of participants invited and eligible to receive BWW or the NHS Choices Moodzone website compared with the expected number of participants (based on estimates from census data in the study area).

Effectiveness: To determine the short-term clinical effectiveness of randomization to BWW versus the Moodzone website on well-being (primary outcome), depression symptoms, anxiety symptoms, social function, and QOL in one locality over 3 months.

Adoption (by services): To determine the number, percent, and representativeness of NHS primary care practices and organizations, secondary care mental health, community and acute trust, third sector, and social care organizations that referred people to either BWW or the Moodzone website.

Implementation: To explore the implementation of the BWW program, including barriers and drivers to reach, effectiveness and adoption, and an economic evaluation of its costs and cost-effectiveness from personal, social, and health care perspectives.

Maintenance: To determine (1) The maintenance of treatment effects on well-being, depressive symptoms, anxiety symptoms, QOL, and social function over 6 months and (2) The take-up by organizations and implementation (number, percentage of BWW across the East Midlands) after the trial has been completed.

We will also explore how the interventions may work by quantitatively examining moderators and mediators of outcome and conducting a qualitative analysis, and in the case of the BWW intervention, discourse analysis.

The discourse analysis aims to answer the following research questions:

How social support is provided within peer support exchanges within BWW?What topics are discussed by trial participants when using BWW?

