### Outcome Measures

Once consented, participants will be asked to complete self-rated questionnaires to measure well-being, depression, anxiety, work and social adjustment, QOL (for economic analysis), receipt of services (for economic analysis), social support, and personality dysfunction (see Table 1). These will be completed online (through the study website) in approximately 20 to 30 min, with the primary outcome data collected first. All data will be stored on the website and downloaded and anonymized by the clinical trials manager.

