#### Secondary Outcomes Measures

Maintenance of well-being 12 and 26 weeks using the WEMWBSGAD-7 scale—completed as part of eligibility at baseline and then at 3, 6, 12, and 26 weeks as a brief measure of the severity of 7 symptoms of anxietyPHQ-9—completed as part of eligibility at baseline and then at 3, 6, 12, and 26 weeks as a measure of depression severity according to the *Diagnostic Statistical Manual, 4th edition* criteria [27]12-item Medical Outcomes Study Short Form health survey version 2.0 (SF-12v2) [28]—a short and practical measure of health-related QOL derived from the longer SF36 that is obtained during interviewSocial support is measured using the 8-item Medical Outcomes Study Social Support Survey (MOS-SS) [29], and it is completed at baselineSocial function on the 8-item Work and Social Adjustment Scale (WSAS) [30]—a simple measure of impact on function, which is attributable to a particular cause such as depression or anxiety. It is completed at baseline and then at 3, 6, 12, and 26 weeks

Mediators of the effectiveness of BWW compared with Moodzone on mental well-being might be the emotional and informational support subscales of the MOS-SS [29]. Data collected by BWW suggest that perceived social support might be an important mediator of outcome, particularly in people experiencing life events and loneliness.

Moderators of outcome at baseline might be the presence of life events in the previous 6 months, measured by the 12-item Brugha Inventory of Life Events [31], and the presence of anxiety alone at baseline. Personality dysfunction will be measured at baseline using the 8-item Standardised Assessment of Personality-Abbreviated Scale (SAPAS) [32]. There may be an interaction between the presence of life events at baseline and greater perceived emotional support from BWW at 3 months and on mental well-being at 6 months, whereas higher scores on the SAPAS may predict dropout and little difference between the treatment arms on mental well-being at 6 weeks.

**Table 1 table1:** Timing and delivery of outcome measures.

Measure	Baseline	3 weeks	6 weeks	12 weeks	26 weeks
WEMWBS^a^	Website	Website	Website	Website	Website
PHQ-9^b^	Website	Website	Website	Website	Website
GAD-7^c^	Website	Website	Website	Website	Website
WSAS^d^	Website	Website	Website	Website	Website
MOS-SS^e^	Website	X^f^	X	X	X
SAPAS^g^	Website	X	X	X	X
Brugha Life^h^	Website	X	X	X	X
SF12-v2^i^	Website	X	X	X	Interview
CSRI^j^	Website	X	X	X	Interview

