^a^WEMWBS: Warwick-Edinburgh Mental Well-Being Scale.

^b^PHQ-9: 9-item Personal Health Questionnaire.

^c^GAD-7: 7-item Generalized Anxiety Disorder Scale.

^d^WSAS: Work and Social Adjustment Scale.

^e^MOS-SS: 8-item Medical Outcomes Study Social Support Survey.

^f^X: Measures are not collected at this time point.

^g^SAPAS: Standardised Assessment of Personality-Abbreviated Scale.

^h^Brugha Life: 12-item Brugha Inventory of Life Events.

^i^SF-12v2: Medical Outcomes Study Short Form health survey version 2.0.

^j^CSRI: Client Service Receipt Inventory.

To explore the reach, adoption, and implementation arms of the RE-AIM framework, a number of process measures will be recorded as the study progresses:

Live log of services, individuals, groups, and charities that are approached to engage with the study. The networks that surround these and how this may spread will be recorded and used to determine reach and adoption. A network of practice comprising all health care stakeholders will be established to explore implementation pathways.Reach will be further explored using Internet analytic software or to derive anonymous data around hit and bounce rates, pages visited, length of visit, type of geography, and simple demographics to the study website can be recorded, downloaded, and analyzedImplementation will be explored when highlighting the barriers and drivers to reach, effectiveness, and adoption assessed through qualitative work with the services, groups, and individuals engaged through recruitment, as well as an economic evaluation of its costs and cost-effectiveness from personal, social, and health care perspectives. In particular, we will explore how participants utilize BWW in relation to the literature on similar websites offering peer support and information for physical illness and literature on social and organizational aspects of depression and anxiety care.Working with the local Academic Health Science Network to record the take-up by organizations and implementation (number, percentage, and representativeness in East Midlands) of BWW across the East Midlands after the trial has been completed should it prove to be clinically and cost effective.

In terms of socioeconomic inequalities, we will record the following provided such detailed recording of information does not deter participation: postcode, age, gender, ethnicity marital status, highest level of education, and employment.

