### Randomization and Monitoring

The treatment to which a participant is assigned will be determined by a computer-generated pseudorandom code using random permuted blocks of varying size by a randomization system embedded within the website. No stratification or minimization is required. The outcome will be single-blind with the clinical trials manager and research associates responsible for the collection, cleaning, and analysis of the data remaining blind to arm allocation until data collection has been completed. Cases of unblinding will be recorded electronically but will not be excluded. Unblinding will only be necessary upon completion of data collection.

Overall, trial monitoring and oversight will be carried out by the CLAHRC-EM Scientific Committee who will act as the trial steering committee and data monitoring committee. The CLAHRC-EM scientific committee is composed of independent experts in statistics, epidemiology, medicine, and patient and public involvement. They will be sent quarterly reports on the status of the study and have the power to recommend or implement changes to the protocol if necessary. They are also able to stop the study if it is deemed unsafe or is failing to recruit after all avenues to recruitment have been exhausted.

There is no planned assessment of safety within the study design, and unless participants report any intercurrent illness or adverse events directly to the study team, it is unlikely that these can be recorded systematically.

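### The 12-week economic data schedule contradicts itself, the 3-month quality-of-life objective has no scheduled data under Table 1, and follow-up resource use and (by inference) SF-12v2 rest on about 200 interview volunteers, 14-15% of those randomised

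*Protocol article*

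**What the plan says.** All references are to the protocol article.

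- **Objectives, Effectiveness:** the effect of randomisation is to be determined "on well-being (primary outcome), depression symptoms, anxiety symptoms, social function, and QOL in one locality over 3 months". The Maintenance objective extends quality of life to 6 months.
- **Secondary Outcomes Measures:** the SF-12v2 is the only quality-of-life instrument listed. Its entry mentions interview and gives no time points.
- **Table 1:** the two rows read "SF12-v2^i^ Website X X X Interview" and "CSRI^j^ Website X X X Interview", for baseline, 3, 6, 12 and 26 weeks in that order. The footnote defines X as "Measures are not collected at this time point".
- **Health Economics:** service use is collected at baseline. Further economic data, including time lost from work, "will be collected during interviews with 200 participants at 12 and 26 weeks who consent to be interviewed". The study will also "measure the participant's own health status using the SF12-v2 during participant interviews". Results are to be given as cost-effectiveness and cost-utility, with an incremental ratio and acceptability curves for Big White Wall (BWW) versus Moodzone.
- **Expected Duration of Participant Participation:** the interview is something that participants may be asked to do.
- **Statistical Analysis:** treatment effects are analysed by intention to treat, with multiple imputation under missing at random.

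**The concern.** There are two linked problems.

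First, the schedule. Table 1 and Health Economics cannot both be right about economic data at 12 weeks. If Table 1 is right, nothing on quality of life is measured between baseline and 26 weeks, so a stated objective cannot be met. An analysis plan cannot repair this later, because data that were not collected cannot be recovered.

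Second, who supplies the data. Agreeing to an interview is a choice that appears to be made after allocation, and it may differ between an arm given a peer-support service and an arm given a link to an information site. If it does, the cost-utility result compares two self-selected groups but will be read as a trial result. Cost-effectiveness is part of the headline aim in the Abstract, and the Strengths section describes the cost-effectiveness estimates as likely to generalise.

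**Working it through.** **1. Schedule, side by side**

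| Source | 12 weeks | 26 weeks |
|---|---|---|
| Table 1, CSRI | not collected | interview |
| Table 1, SF-12v2 | not collected | interview |
| Health Economics, economic data | interview | interview |
| Health Economics, SF-12v2 | interview, no time point given | interview, no time point given |
| Objectives, quality of life | needed (over 3 months) | needed (over 6 months) |

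The conflict is explicit for economic data (CSRI). For the SF-12v2 the conflict is between Table 1 and the 3-month objective.

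**2. The plan's own sample size**

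Inputs from Sample Size and Justification: difference 3, SD 12, two-sided 5%, power 90%, zero pre-post correlation, 50% loss.

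- Normal approximation: n per arm = 2 × (1.960 + 1.282)² × 12² / 3² = 336.2, rounded up to 337.
- The t-based version gives 337.2, rounded up to 338 per arm, or 676 in total. This matches the plan.
- 676 / (1 − 0.5) = 1352. This also matches.

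No such justification is given for the 200 interviewees.

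**3. Coverage**

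- 200 / 1352 = 14.8%.
- 200 / 1400 (the expected recruitment) = 14.3%.
- About 85% of randomised participants therefore have no follow-up CSRI by design, before any attrition.

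**4. Precision** (assumption: interviewees split equally, 100 per arm)

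- SE in SD units = √(2/100) = 0.141, so the 95% CI half-width is 1.96 × 0.141 = 0.28 SD.
- Detectable difference = (1.960 + 0.842) × 0.141 = 0.40 SD at 80% power, and (1.960 + 1.282) × 0.141 = 0.46 SD at 90%.
- Power for 0.25 SD (the trial's own 3/12) = Φ(0.25/0.141 − 1.96) = 42%. At 338 per arm it is 90%.
- If only 50 per arm are retained (assumed), power is 24%.

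**5. Selection, as an illustration** (all values assumed)

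The true arm difference is zero, 14.8% consent in each arm, and consent is unrelated to outcome in one arm. In the other arm the log-odds of consent rise by β per SD of outcome. To first order, the mean among those consenting shifts by β × (1 − 0.148).

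| β | First-order shift (SD) | Simulated shift (SD) |
|---|---|---|
| 0 | 0 | 0.00 |
| 0.25 | 0.21 | 0.21 |
| 0.50 | 0.43 | 0.41 |

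A moderate dependence in one arm is enough to produce a spurious difference about the size of the 0.25 SD that the trial is built to detect.

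**6. Effect on QALYs of having no 12-week value**

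This assumes that cost-utility uses QALYs by the trapezium rule, with a gain g at 26 weeks. Areas are in units of g/52.

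| Assumed path of the gain | True area | Baseline + 26 weeks | Adding 12 weeks |
|---|---|---|---|
| Full by week 6, then held | 3 + 20 = 23 | 13 (−43%) | 6 + 14 = 20 (−13%) |
| Linear to week 26 | 13 | 13 (0%) | 13 (0%) |
| Nil to week 12, then linear | 14/2 = 7 | 13 (+86%) | 7 (0%) |

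The sign and size of the error depend entirely on the path.

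**The case against.** The case on the other side is substantial, and several stronger readings fail.

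- **All follow-up costs come from 200 people.** A reader might infer this, but the documents do not support it. Technology and licence costs do not come from interviews, BWW records log-ins and time on site, and all participants are asked about other mental health resources used. A cost-effectiveness ratio could also use WEMWBS, collected online from everyone. What depends on the interviews is participant-reported resource use on the CSRI and lost time. The number 200 is attached to economic data, and that the SF-12v2 comes from the same interviews is a strong inference rather than a statement.
- **Outcome Measures contradicts Table 1.** The sentence "These will be completed online (through the study website) in approximately 20 to 30 min" follows a reference to participants who have just consented, and Table 1 does put every measure on the website at baseline. No conflict is shown.
- **The interviews break the blind.** Staff are to be "remaining blind to arm allocation until data collection has been completed", and the qualitative interviews are arm-specific. However, the article does not say that the economic and qualitative interviews are the same, or who conducts them.
- **Intention to treat is impossible.** It is weakened, not excluded. Analysis as randomised with imputation can be done, but it leans heavily on missing at random when about 85% are absent through volunteering.
- **QALYs are under-counted by 43%.** This needs an early, sustained gain. The Background reports that in the earlier peer-support trial of 311 people quality of life improved only at 6 months, which points the other way.
- **Standard errors are 1.84 times larger than with web collection.** √(676/200) = 1.84 borrows the number evaluable at 6 weeks. The article gives no 26-week response rate, and with fewer web responders the ratio shrinks.

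It is also fair to say that how interviewees are chosen may be set out in the full protocol, that differential consent is plausible but undocumented, and that web follow-up with 50% loss is itself self-selection. None of this removes the schedule conflict or the missing 3-month data.

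**Conclusion.** The point stands in this form and should be fixed. The primary outcome, its sample size and its analysis are unaffected, so it does not threaten the main result.

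Two things follow from the text alone: Table 1 and Health Economics disagree on economic data at 12 weeks, and under Table 1 the 3-month quality-of-life objective has no data. A third follows with one inference, that the SF-12v2 is taken in the same interviews: after baseline the quality-of-life and cost-utility comparison rests on 14-15% of randomised participants, who are included because they agreed to be interviewed. That comparison is not protected by randomisation. Allocation was random, but membership of the analysed subset was not. A random, arm-balanced subsample would lose only precision, but the article describes none.

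The 42% power figure assumes an equal split of 100 per arm. The bias figures are illustrative, and the bias is zero if consent is unrelated to outcome in both arms. No single QALY error can be quoted.

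**What to change.** 1. **Reconcile the text.** Make Table 1, the Effectiveness objective, the SF-12v2 entry under Secondary Outcomes Measures, and Health Economics agree on time points, mode and who is asked. This costs only an amendment.
2. **Preferred:** collect the SF-12v2 and CSRI (a short form if needed) on the website at 12 and 26 weeks from all randomised participants, after WEMWBS, and analyse them as randomised with the planned imputation. The website already administers both at baseline and other measures at those visits, so the work is a protocol amendment and some programming. The price is a longer questionnaire at visits that carry WEMWBS maintenance, PHQ-9, GAD-7 and WSAS. Web attrition remains and should be reported by arm. Moving only the SF-12v2 would be lighter, but it would leave resource use, and so the incremental ratio, in the volunteer subset.
3. **If that is not adopted:** either draw the interview subsample at random, stratified by arm, and report refusals by arm; or drop the 3-month quality-of-life objective and present interview-based quality of life and cost-utility as exploratory results in a volunteer subset.

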### Qualitative Analysis

Qualitative interviewing and analysis will be used to determine the barriers and motivations for participant engagement in the study to inform and further develop the study’s engagement strategy. We also intend to explore participants’ experiences of taking part in the study to gain and understand the motivations for use of online peer support. For those in the BWW arm of the study, this will include patterns and levels of engagement (eg, active user vs “lurker”), negative experiences and beliefs about efficacy, and role in personal empowerment. For those in the Moodzone arm, we will interview participants about negative and positive experiences of receiving just information in relation to managing depression and anxiety. Qualitative interviews will be sought with a maximum variance sample based on sociodemographic factors, scores on baseline clinical measures, and whether or not they are using other health services. Participants will be contacted after they have been in the study for 6 weeks. We will also interview those who did not wish to participate or dropped out but indicated they wished to be contacted to leave feedback.

### Participant Messages

All conversation threads over 6 months in which at least one message has been posted by a trial participant will be retrieved by BWW and sent securely and anonymously to the research team. These will include messages posted by nonstudy participants. However, these messages will not be analyzed; rather they are provided to understand the context of the messages posted by the study participants.

The data generated for this phase will be analyzed using content analysis [39]. This approach is frequently used to quantify theoretical concepts and qualitative data categories in the manifest content of large volumes of textual information and has been successfully employed in previous studies [40-42]. We will address the discourse analysis questions as follows:

How social support is provided within peer support exchanges within BWW?

We propose to employ the Social Support Behavior Code [43] as our guiding theoretical framework. This framework has been used extensively in the analysis of online forum communication (eg, [43]) and provides the means to identify and quantify the presence of five key categories of social support: information support, emotional support, network support, esteem support, and tangible assistance. Our analysis will record separately the number of requests for support as well as the provision of support, by category (above), within the dataset.

What topics are discussed by trial participants when using BWW?

We propose to use thematic analysis to address this research question using previous guidelines [44]. This approach allows the systematic analysis of textual data to identify and describe emergent themes based on patterns within the dataset.

